### Statistical analysis

Basic descriptive statistics will be calculated for baseline variables, and according to trial arm (BMI vs. control). Intention-to-treat (ITT) analysis will be based on available data from all randomized patients at 3 and 6 month follow-up. In case of missing follow-up values multiple imputation will be performed [85]. For primary and secondary hypotheses we will use linear mixed models adjusted for baseline differences to examine differences between intervention and control group with intervention condition as fixed effect and clusters (hospital on a weekend) as random effect. The two-sided ?-level is set to 0.05. Additional analysis will be conducted on a per-protocol analysis set. Process data on intervention delivery, implementation and receipt will be analyzed in subsequent steps.

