### Randomization

Because of limited resource availability, individual level random assignment of eligible participants to BMI or control condition is not feasible in this study. Instead a stratified cluster randomization is deemed appropriate with weekends (N = 129) as stratum and hospital (N = 6) on a weekend as unit of randomization. Over a data collection period of 30 months this yields a total of N = 774 possible clusters. This approach leads to a high number of clusters, which is highly recommended [83] and assures that at each weekend patients in one half of the hospitals are assigned to the BMI and the other half to the control condition. The total amount of possible combinations between strata and hospitals is balanced in a way that each clinic acts equally often as control and BMI condition and assures that all clinics are either control or BMI condition at each weekend. The resulting randomization plan was established prior to the data collection process by a research assistant from the Department of Medical Biometry and Epidemiology (University Hospital Hamburg-Eppendorf) who is not involved in the project, using the statistical software package SAS, Version 9.3 [84].

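### The stated model omits the weekend and hospital factors that structured the randomisation; the effect is small and conservative, and the repair is cheap

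*Protocol article*

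**What the plan says.** **Design (Protocol article, Randomization).** Allocation is by cluster, "with weekends (N = 129) as stratum and hospital (N = 6) on a weekend as unit of randomization". Two restrictions apply. Within a weekend, "at each weekend patients in one half of the hospitals are assigned to the BMI and the other half to the control condition". Over the whole trial, "each clinic acts equally often as control and BMI condition". With 129 weekends and six hospitals, "this yields a total of N = 774 possible clusters".

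**Model (Protocol article, Statistical analysis).** Primary and secondary hypotheses are tested with "linear mixed models adjusted for baseline differences", "with intervention condition as fixed effect and clusters (hospital on a weekend) as random effect". The baseline variables are not named. No section of the article makes weekend or hospital a term in the model.

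**Clustering assumption (Protocol article, Sample size).** The intra-cluster correlation is 0.05, the mean cluster size is 1.264 patients, the design effect is 1.013 and the total sample is 312. Clusters without patients are left out of the analysis.

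**The concern.** A restriction on the randomisation removes variation from the comparison of arms. Here, differences between weekends largely cancel because both arms are represented every weekend, and differences between hospitals largely cancel because each hospital serves in both arms equally often. An analysis recovers that gain only if it has terms for those factors.

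The single random intercept does not do this. A hospital-by-weekend intercept treats two hospitals on the same weekend as independent, and likewise two weekends at the same hospital. Any lasting difference between the six hospitals, or any calendar effect over 30 months, is therefore counted as noise in the treatment comparison although the design has controlled for much of it. The result would be intervals somewhat wider than the design warrants, and some loss of power, on all three primary outcomes.

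**Working it through.** **Inputs from the article:** 129 weekends, 6 hospitals, 312 patients, intra-cluster correlation (ICC) 0.05, mean cluster size 1.264.

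**Assumptions:** outcome SD of 1, additive variance components, and patients arriving at random over the hospital-weekend slots. The article gives no split of the ICC, so the full range is shown.

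**Step 1. The plan's design effect.** 1 + (1.264 − 1) × 0.05 = 1.0132, which reproduces the stated 1.013.

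**Step 2. What the ICC contains.** Two patients in the same hospital on the same weekend share the hospital effect, the weekend effect and the hospital-by-weekend effect. The ICC of 0.05 is therefore the sum of the three variance shares: hospital + weekend + hospital-by-weekend = 0.05.

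**Step 3. The two ends by hand.**
- With 312 patients over 774 slots the mean is 312/774 = 0.403 per slot. Under random arrival a patient has on average 0.403 others in the same cluster. (This gives 1.215 patients per non-empty cluster, close to the plan's 1.264.)
- Standard error (SE) without clustering: √(4/312) = 0.1132.
- Planned model: 0.1132 × √(1 + 0.403 × 0.05) = 0.1132 × √1.0202 = 0.1144.
- Cost of five hospital contrasts, through chance imbalance among enrolled patients: a variance factor of about 1/(1 − 5/311) = 1.0163.
- *All variance between hospitals:* the hospital terms remove the 0.05, so SE = 0.1132 × √(0.95 × 1.0163) = 0.1113. Ratio 0.1113/0.1144 = 0.973, or −2.7%.
- *No variance between hospitals or weekends:* only the cost remains. √1.0163 = 1.008, or +0.8%.

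**Step 4. The range between.** Generalised least squares with known variance components, averaged over simulated 129 × 6 schedules (three hospitals per arm each weekend, about 312 patients), compares the planned model's SE with that of a model with hospital fixed and with weekend and cluster random:

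| Split of the total ICC of 0.05 | Change in SE |
|---|---|
| All hospital | −2.7% |
| Half hospital, half weekend | −1.5% |
| Three equal shares | −0.7% |
| All weekend | −0.4% |
| All hospital-by-weekend | +0.8% |

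The actual type I error of the planned model over these splits is 0.047 to 0.050.

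**Step 5. The same range in patients.** −2.7% is worth 312 × (1/0.973² − 1) ≈ 18 extra patients. +0.8% costs 312 × (1 − 1/1.008²) ≈ 5.

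**Step 6. What a larger gain would need.** With hospital, weekend and hospital-by-weekend at 0.05 each (total ICC 0.15) the SE falls from 0.1162 to 0.1117, about 4%. With shares of 0.10, 0.10 and 0.05 (total ICC 0.25) it falls from 0.1186 to 0.1087, about 8%.

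**The case against.** The strongest reply is that little is at stake. The random effect sits on the unit of randomisation, which is the term that validity most needs. Both omitted factors are balanced against arm by design, so leaving them out errs on the safe side. The six hospitals are in one city and one mobile team delivers the intervention, so a large hospital effect is not evident. The article gives the model in one sentence, and a fuller covariate list may stand in an analysis plan that is not shown. All of this stands as an argument about size. It does not remove the mismatch: the article itself names the model's effects, and adjustment for baseline differences does not naturally cover design factors that are balanced on purpose.

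A reader might infer three stronger points, which the article does not support.

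- *That the precision gained by the design is largely lost.* Reductions of 4% to 8% in the SE need total ICCs of 0.15 to 0.25, three to five times the plan's figure.
- *That the estimate is biased or the test invalid.* The balance described under Randomization rules this out as a consequence of the omission.
- *That the cluster intercept is unsuitable because most clusters are single patients.* They are: with a mean of 1.264 and no empty clusters, at most 26.4% can hold two or more patients, so at least 73.6% hold one. The variance is therefore weakly estimated, but with a design effect of 1.013 a zero estimate hardly changes the SE. The repair keeps this term and does not make it better estimated.

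**Conclusion.** The point holds as a mismatch between the stated design and the stated model, with a small effect. If hospital or weekend variance exists, the planned standard errors are slightly too large. There is no bias and no inflation of type I error. At the plan's own ICC of 0.05, adding the design factors changes the SE by about −2.7% to +0.8%, depending on how that correlation divides among hospital, weekend and their combination, which the article does not say. The range rests on additive variance components treated as known, random arrival of patients and about 312 analysed patients. The change is worth making because it is nearly free and ties the analysis to the randomisation in advance, not because the trial's conclusion is likely to turn on it.

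**What to change.** State the model for each primary outcome as: follow-up outcome on arm + baseline value of that outcome + hospital (six-level fixed effect) + random intercept for weekend + random intercept for hospital-by-weekend.

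Weekend should be random. With 312/129 = 2.4 patients per weekend, fixed weekend terms would use too many degrees of freedom.

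**Cost:** a change of wording, five degrees of freedom for hospital and one further variance component. Hospital and weekend are known for every patient, so no data are added and the sample size does not change. If hospitals and weekends do not differ, the SE may rise by just under 1%.

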## Discussion

In this study protocol we present the design and current implementation of a randomized-controlled trial which aims at evaluating the effectiveness of the indicated *HaLT-Hamburg* intervention for children and adolescents following treatment due to AAI in the ED. Beside a rigorous trial design with focus on relevant alcohol-related outcomes, we include additional evaluative components to address important issues of feasibility and practical implementation under “real-world” conditions in an ED-setting.

### Strengths and limitations

The study has a number of significant strengths. First and foremost, a rigorous evaluation of this intervention is timely because *HaLT* interventions are already widely applied in Germany in different modulations. *HaLT* interventions are brief and based on MI, which has been proven effectiv for reducing alcohol-related problems [64,86]. Previous study results are promising [54,56-58], yet difficult to generalize and full scale trial evaluations including process and implementation evaluation are missing to date. Overall, with our study we contribute to the literature mainly because studies addressing effectiveness of BI’s in the ED with a focus on minors hospitalized following an alcohol-related event are scarce [[name], [name], [name], [name]: *Brief Interventions for Alcohol-involved Adolescents in Emergency Care: A Systematic Review,* forthcoming] and most existing RCT’s in the ED setting have been conducted in the U.S., leaving uncertainty whether results generalize to other countries [87]. To our knowledge we are the first to target adolescents in the ED immediately after the experience of an AAI. This approach appears promising due to a presumed “teachable moment” arising from the potentially life-threatening experience of AAI leading to hospitalization. This experience provides a window of opportunity for initiating behavior change in minors who have elevated risks for repeated AAI episodes if untreated [4] and who are in a developmental stage in which risk behaviors are normative which may limit responsiveness to MI or brief advice in other settings [88].

Another strength is the integration of additional evaluative components via a comprehensive process evaluation which qualifies *HaLT-Hamburg* as a pragmatic trial [89,90] and raises external validity. In the considerations guiding our study we aimed at minimally interfering with “real world” conditions, as indicated by applying rather unrestricted inclusion (access-to-care) criteria, unobtrusive measures for intervention fidelity monitoring, employing facilitators who will continue working in the project after data collection has ceased (as opposed to research assistants) and a number of other aspects associated with implementation and intervention delivery. For example, while intervention, telephone booster and training sessions are manual-based and replicable, facilitators are left with a certain leeway in intervention delivery to allow tailoring of the intervention to the patient’s needs in order to adhere to MI spirit [64]. This may pose a limiting factor for internal validity. However, we included measures for manual adherence and MI-fidelity as well as clients’ ratings of perceived facilitator’s MI skills. A second possible limiting factor is that our data are based on self-reports. However, this approach is widely used in comparable studies [24] and previous studies indicate that adolescent self-reports on substance use are reasonably valid [91,92].

### Implications for practice

As mentioned above, our study addresses a number of practical aspects. Importantly, actions for setting up organizational structures to implementation involving relevant stakeholders have been considered from the beginning of the project. This way, funding of ED external trained facilitators could be assured by partnering health insurances during the study period and with a clear perspective of further funding if our intervention proves effective. Moreover, our study is embedded in *psychenet: the Hamburg Network for Mental Health*[93] with over 60 partners from research, health care, health industry and government in the Free and Hanseatic City of Hamburg. This network provides a strong structural resource for further implementation. *HaLT-Hamburg* is thus well embedded and supported by communal structures, is implemented under “real world” clinical conditions and is therefore suited to reveal important information on possible barriers and resources for practical implementation [60,94] in addition to insights on effectiveness and conditions influencing effectiveness of the HaLT-Hamburg BMI.

## Conclusion

Our study addresses a highly relevant target group and contributes to the current literature on brief interventions by filling apparent gaps. The study will provide insights about effectiveness of the *HaLT-Hamburg* intervention and hence about a promising approach of targeted interventions for adolescents experiencing AAI. Moreover, we integrated the evaluation of practical implications and address important elements of translational research as well as actions needed to sustainably implement BI’s under practical conditions, an issue often neglected in prior research.

## Abbreviations

AAI: Acute alcohol intoxication; BI: Brief intervention; BMI: Brief motivational intervention; ED: Emergency department; MI: Motivational interviewing; TAU: Treatment as usual
